#### Primary outcome measures

1. **Rating Anxiety in Dementia** (RAID) [24]. This rates signs and symptoms of anxiety using interviews with carers and people with dementia. There are 18 questions in four categories: worry, apprehension, vigilance, motor tension and autonomic hypersensitivity. A score of 11 or above indicates significant clinical anxiety. It has good inter-rater and test-retest reliability, is sensitive to change and correlates with quality of life [25].

2. **Clinical Services Receipt Inventory** (CSRI) [26]. A tool that collects information about the interviewee’s use of health and social care services, accommodation and living situations, income, employment and benefits, and any changes that may be incurred in the receipt of these services (after the therapy).

#### Secondary outcome measures

3. **Mood**: Hospital Anxiety and Depression Scale (HADS) [27]. The HADS is a widely used measure of anxiety and depression validated for all age groups.

4. **Quality of life** (QOL): Quality of Life-Alzheimer’s Disease (QOL-AD) [28]. This is a self-report measure for the person and their carer, with 13 items covering domains including physical health, energy, friends and fun. It has excellent inter-rater reliability and internal consistency, and good content, criterion and construct validity.

5. **Behavioural disturbance**: Neuropsychiatric Inventory (NPI) [29]. This assesses ten areas including delusions, hallucinations, dysphoria and agitation/aggression. Content and concurrent validity, inter-rater and test-retest reliability and internal consistency are all good.

6. **Cognitive function**: Mini-Mental State Examination (MMSE) [30]. This is an internationally recognised, 11-item set of simple tasks presented to the participant including orientation to time and place, attention, recall, language and visual construction. It has a maximum score of 30 points, with 24 or less suggesting cognitive impairment. Reliability and validity are satisfactory.

7. **Depression**: Cornell Scale for Depression in Dementia [31]. This rates depression in five categories including mood-related signs, behavioural disturbance and ideational disturbance, using information from interviews with staff and participants. Good reliability and validity have been demonstrated.

8. **Person****carer relationship**: Quality of Caregiver and Patient Relationship (QCPR) [32]. This is a 14-item scale measuring relationship quality including the level of criticism and level of warmth, rated by both the person and their carer. Good reliability and validity have been demonstrated.

9. **Carer mood**: Hospital Anxiety and Depression Scale (HADS) [27].

#### Qualitative interviews

After follow-up 1, 12 patient-carer dyads who received CBT will be invited to take part in qualitative interviews, led by another research assistant (to ensure blindness to treatment) and lasting approximately 1 hour. Issues addressed will include experiences of the sessions, views on themes and techniques, and benefits/changes identified in everyday life. Interviews will be audio recorded and transcribed. Framework analysis [33] will be used to extract themes and draw conclusions.

#### Treatment implementation strategies

Treatment implementation (TI) strategies are recommended to ensure that treatment has been delivered, received and enacted as intended [34]. We will employ several methods to monitor treatment delivery and receipt: (1) the training and manual; (2) an adherence checklist devised in the manual, developed for the purpose of the study; (3) by audio recording all sessions, of which a random sample will be checked by GC for adherence to the manual. Treatment receipt and enactment will also be explored through qualitative interviews.

#### Statistical analysis

As this is a pilot trial, our main aims in evaluation will be to record response to recruitment, acceptability of randomisation, retention in therapy, attrition, prescribing of anxiolytics, any negative effects, extent/distribution of missing data and basic costs. We will conduct exploratory statistical analyses as our sample size will limit definitive conclusions. Data will be analysed by SPSSv16 using 'intention to treat'. Differences in outcomes between the two arms of the RCT over time will be modelled using generalised estimating equations, taking into account potential clustering due to using several therapists. We will also conduct exploratory analyses of factors predicting treatment outcome such as anxiolytic medication, age, dementia severity, treatment preference and number of sessions received. The confidence intervals around the effect size for the primary outcome, anxiety, will help us to estimate the sample size required for a full-scale trial.

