### Phase 11: Intervention phase

#### Design

The design is a single-blind, multicentre, pilot RCT of CBT plus treatment as usual (TAU) versus TAU for people with dementia. Patient-carer dyads will be randomly allocated to either CBT or TAU. As no trials have been done in this area, we were unable to estimate the likely effect size of this intervention. We will recruit 50 participants with power set at 80%, *p* = 0.05. This will be adequate to detect an effect size of 0.8 or above. An objective of this study is to provide data on the actual effect size of the intervention in order to do a power analysis for a definitive RCT. Figure 1 shows the trial design.

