#### Participants

Fifty participants and their carers will be recruited through North East London Foundation Trust (NELFT) and North Essex Partnership NHS Foundation Trust (NEPFT). Recruitment will be through memory services, community mental health teams, admiral nursing teams and outpatient referrals.

Inclusion criteria are:

1. Meet DSM-IV criteria for dementia in mild to moderate range, Clinical Dementia Rating (CDR) [23] score of 0.5, 1 or 2.

2. Clinical anxiety, as determined by a score of 11 or above on the Rating Anxiety in Dementia scale (RAID) [24].

3. Living in the community.

4. The presence of a carer who is willing to participate in the therapy.

5. An ability to understand and communicate in English.

6. Willing to engage in therapy involving discussion of thoughts and feelings.

Exclusion criteria are:

1. Co-morbid psychiatric disorder (e.g. psychosis) or challenging behaviour (e.g. severe agitation) likely to prevent engagement in therapy.

2. Presence of a learning disability or severe physical illness that could impact on participation.

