#### Randomisation

Randomisation will be conducted by telephoning an independent administrator within PRIMENT Clinical Trials Unit after the participant/carer has provided informed consent and baseline data. The randomisation schedule is being developed by an independent statistician in PRIMENT, and blocking will be employed (with block sizes varying between 4 and 6) to help ensure equal numbers in the intervention and control arms.

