#### Outcome measures

All outcome measures will be administered by the main research assistant, blind to group allocation, at week 1 (baseline), week 15 (follow-up 1) and 6 months (follow-up 2). Fifteen weeks for follow-up 1 was determined by the field-testing phase, which suggested that it takes an average of 15 weeks to complete a ten-session intervention because of factors such as randomisation time, illness and holiday. Demographics and general information will be collected including age, gender, ethnic group, use of medication (including anxiolytics and cholinesterase inhibitors), treatment preference and participation in other activities. The Clinical Dementia Rating (CDR) [23] will be used to provide a global rating of dementia severity as part of the general background information.

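### No conditioning on baseline RAID is stated for the GEE. If baseline enters as a repeated response with free arm means, adjusting for it would cut the variance by about 15–35% (assumed correlation 0.7–0.3).

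*Protocol article*

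**What the plan says.** The Randomisation section places allocation "after the participant/carer has provided informed consent and baseline data", so baseline RAID cannot be affected by treatment. The Outcome measures section has every measure taken "at week 1 (baseline), week 15 (follow-up 1) and 6 months (follow-up 2").

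The Statistical analysis section then gives the between-arm model: "Differences in outcomes between the two arms of the RCT over time will be modelled using generalised estimating equations". The one thing it says the model will allow for is clustering by therapist. A separate exploratory analysis of predictors lists anxiolytic use, age, dementia severity, treatment preference and sessions received. Baseline anxiety is in neither place. The section does not say whether baseline RAID is a covariate, one of the repeated responses, or unused.

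The same section calls the statistical analyses exploratory, but gives the interval around the anxiety effect a job: helping to set the size of a full trial. The Design section also makes the effect size an objective. Its sample size statement is "power set at 80%, *p* = 0.05", followed by "This will be adequate to detect an effect size of 0.8 or above".

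**The concern.** A model of arm differences over time, with a baseline visit among the measurement times, is often fitted with arm, visit and their interaction, all visits being responses. Each arm then has its own free baseline mean, and the treatment effect at a follow-up visit is a difference in change from baseline. In a randomised trial the arms have the same expected baseline, so estimating a separate baseline mean for each arm spends information needlessly. Conditioning on baseline is never less precise than this contrast when the variances at the two visits are equal.

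At stake is the width of the RAID interval. With about 25 people per arm it will be wide under any analysis, and it is the pilot's stated quantitative input to the next trial.

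**Working it through.** **Inputs.** Total 50, 80% power, p = 0.05 and effect size 0.8 come from the Design section. Equal arms come from the Randomisation section ("to help ensure equal numbers in the intervention and control arms"), so 25 per arm. The correlation r between baseline and follow-up RAID is not in the document; I assume 0.3 to 0.7. I also assume equal SDs at baseline and follow-up, and complete data.

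**Step 1: the plan's own figure.** Two-sided normal approximation: n per arm = 2(1.96 + 0.842)²/0.8² = 24.5, rounded up to 25, total 50. At 25 per arm, 0.8 × √(25/2) = 2.83 and 2.83 − 1.96 = 0.87, which gives 80.7% power. With the t distribution it is 25.5 per arm, and 79.1% power at 25. The stated 50 reproduces as an unadjusted two-sample comparison.

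**Step 2: variance of the RAID effect at one follow-up visit**, relative to comparing follow-up scores alone (= 1):

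- Arm-by-visit model with free baseline means: 2(1 − r).
- Baseline-adjusted: 1 − r².
- Ratio, adjusted to arm-by-visit: (1 − r²)/[2(1 − r)] = (1 + r)/2, so the saving is (1 − r)/2.

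The effect detectable with 80% power is 2.80 × √(2/25) = 0.79 SD, multiplied by the square root of the relative variance.

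| r | Arm-by-visit | Adjusted | Ratio | Saving | Detectable, arm-by-visit | Detectable, adjusted |
|---|---|---|---|---|---|---|
| 0.3 | 1.40 | 0.91 | 0.65 | 35% | 0.94 | 0.76 |
| 0.4 | 1.20 | 0.84 | 0.70 | 30% | 0.87 | 0.73 |
| 0.5 | 1.00 | 0.75 | 0.75 | 25% | 0.79 | 0.69 |
| 0.6 | 0.80 | 0.64 | 0.80 | 20% | 0.71 | 0.63 |
| 0.7 | 0.60 | 0.51 | 0.85 | 15% | 0.61 | 0.57 |

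In interval width, √0.65 = 0.81, √0.75 = 0.87 and √0.85 = 0.92: the adjusted interval is about 19%, 13% and 8% narrower at r = 0.3, 0.5 and 0.7.

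Below r = 0.5 the change contrast is less precise than ignoring baseline altogether, since 2(1 − r) exceeds 1. Entry is restricted to RAID of 11 or above (Participants section), which could lower r. That would make the arm-by-visit reading worse, not better.

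**Step 3: simulation check.** 25 per arm, three visits, exchangeable correlation, 1,000 runs; variance of the week-15 effect relative to 2/25:

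| r | Arm-by-visit GEE | Common-baseline GEE | Baseline as covariate |
|---|---|---|---|
| 0.4 | 1.17 | 0.83 | 0.84 |
| 0.5 | 1.01 | 0.78 | 0.80 |
| 0.6 | 0.82 | 0.67 | 0.67 |

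The simulation error of a variance from 1,000 runs is about √(2/1000) = 4.5%, so these agree with the formulas. A GEE with a common baseline mean is as precise as covariate adjustment, so the loss under that reading is about zero.

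**Step 4: cost of the covariate.** Estimating one slope in 50 people inflates the variance by about 1 + 1/(50 − 4) = 1.02, small beside the 15–35%.

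**The case against.** The strongest reply is that the article is silent on this, and silence is not a decision. A model over time fits at least three specifications: follow-up visits as responses with baseline as a covariate; three visits with a common baseline mean; and three visits with free baseline means. Only the third carries the loss calculated here. Covariates and mean structure are commonly left to a full protocol or analysis plan that is not shown. The analyses are labelled exploratory, and the main aims are recruitment, retention, attrition and similar feasibility measures.

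Most of this stands. It means the point is not an error in the plan, and the range of possible loss starts at zero. It does not remove the recommendation. The section goes as far as naming the model and one thing it allows for, the anxiety interval has a stated planning use, and a more precise form is available from data already collected.

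Three stronger readings are tempting and are not supported:

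- **That the plan rejects baseline adjustment.** It does not mention it either way.
- **That the effect is diluted to two thirds.** This would follow from a single arm effect pooled over all three visits, one of them before treatment. The plan does not propose such an effect.
- **That centre is unbalanced by design.** Recruitment is through two trusts, "North East London Foundation Trust (NELFT) and North Essex Partnership NHS Foundation Trust (NEPFT"), and only blocking is described. An article may omit stratification, so its absence cannot be inferred.

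**Conclusion.** The concern holds conditionally. No conditioning on baseline RAID is stated. On the arm-by-visit reading with free baseline means, adjustment would save (1 − r)/2 of the variance: about 15% at r = 0.7 and 35% at r = 0.3. The figure rests on an assumed r, on equal SDs at the two visits and on that reading of the model. If baseline is already a covariate, or the baseline mean is common to both arms, there is nothing material to gain.

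A reader might infer that the sample size is wrong or that the trial is underpowered. Neither follows: 50 reproduces for an effect of 0.8 without any baseline adjustment. What may suffer is the precision of the interval carried forward to the definitive trial.

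**What to change.** In the Statistical analysis section, state that RAID at 15 weeks and 6 months is the response, with baseline RAID as a covariate and arm, visit and arm × visit as effects. A model with all three visits as responses and a baseline mean constrained to be equal in the two arms is an equally good choice. Name the follow-up visit at which the effect and its confidence interval are read. Treat each secondary scale that has a baseline in the same way, using its own baseline value. Adjusting for centre is optional.

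The cost is one degree of freedom and a change of analysis wording. No new data, visits or participants are needed, and the sample size statement can stay as it is.

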#### Interventions

CBT plus TAU: The patient-carer dyads will participate in 10 weekly sessions, each lasting 1 h hour. This number was determined on the basis of the published literature, the team’s experience and patient and carer feedback.

The manual is divided into four phases. Phase 1 involves assessment and formulation. Key aims are to build a collaborative relationship, socialisation to the CBT model, identifying goals and establishing the involvement of the carer. The carer’s role is to support the person with dementia in implementing strategies, for example applying what has been discussed during sessions in everyday life. Their involvement could range from very little (e.g. attending brief parts of some sessions) to being present at all times. Phase 2 involves the application of change processes, which the therapist will adapt according to the needs and strengths of the individual. These include identifying and practicing strategies for feeling safe, identifying and challenging unhelpful cognitions, ‘realistic negative automatic thoughts’, calming thoughts (on cue cards) and behavioural experiments. Phase 3 works on ending the therapy and developing a blueprint for the future. This includes reviewing and consolidating learned skills, integration of skills into everyday life and considering the future involvement of carers and others.

Sessions will cover themes and broad ideas, but there will be specific guidelines on how to adapt them to suit the needs of individuals. For example, the degree to which ‘cognitive’ and ‘behavioural’ elements are used will vary, with higher functioning participants being more able to access the ‘cognitive’ and a greater emphasis on behavioural aspects with the more impaired.

For some, sessions may need to be shortened or breaks may be required to maximise attention.

Telephone contact will be offered between sessions to answer questions and encourage ongoing work, should it be required. Sessions will be delivered by clinical or counselling psychologists, with experience of working with people with dementia. They will be given regular clinical supervision by a senior old age clinical psychologist with specialist CBT training.

Treatment as usual (TAU): This is defined as the standard treatment available to people with anxiety and dementia, which is most likely to include medication or no treatment.

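### Uncorrected GEE with a few therapists, all in the CBT arm, would give confidence intervals for the RAID difference that are somewhat too narrow

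*Protocol article*

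**What the plan says.** The Statistical analysis section of the protocol article fixes the model: outcomes in the two arms over time are "modelled using generalised estimating equations, taking into account potential clustering due to using several therapists". It names SPSS v16 and intention to treat. It calls the statistical analyses exploratory, and adds that the confidence interval around the anxiety effect size will inform the sample size of a full-scale trial.

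The source of clustering is in the Interventions section: "Sessions will be delivered by clinical or counselling psychologists, with experience of working with people with dementia". TAU is described as standard care, "which is most likely to include medication or no treatment". The Design section confirms the comparison: "The design is a single-blind, multicentre, pilot RCT of CBT plus treatment as usual (TAU) versus TAU". Trial therapists therefore exist in one arm only.

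On size, the Design section says "We will recruit 50 participants with power set at 80%, *p* = 0.05", and "This will be adequate to detect an effect size of 0.8 or above". Blocked randomisation is used "to help ensure equal numbers in the intervention and control arms", so about 25 participants per arm.

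The article does not state the number of therapists, the GEE cluster unit, the working correlation, the variance estimator, the reference distribution, or whether a small-sample correction applies.

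**The concern.** The robust variance of GEE is justified for many independent clusters. If therapist is the cluster, the CBT arm supplies only as many clusters as there are therapists, and the article calls these "potential clustering due to using several therapists". Two things then go wrong together. The variance estimate for the CBT arm is biased downward. It is also unstable, so a normal reference is too short.

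Clustering on participants instead avoids most of the small-cluster problem, but it leaves out the therapist effect that the plan says it will take into account.

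The output at stake is the interval for the RAID difference. An interval that is too narrow would make the pilot's effect size look better known than it is when the definitive trial is planned.

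**Working it through.** **1. The plan's own figure.** With effect size 0.8, SD 1, two-sided 5% (sidedness is not stated; two-sided assumed) and 80% power: n per arm = 2 × (1.960 + 0.842)² / 0.8² = 24.5, rounded up to 25, so 50 in total. The normal formula gives 80.7% power at 25 per arm, and the t-test gives 79.1%. The stated size is reproduced. It contains no allowance for therapist clustering.

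**2. Inputs for the check.** From the article: 25 per arm, therapists in the CBT arm only. Assumed: k therapists (2 to 8), near-equal caseloads m = 25/k, ICC ρ from 0 to 0.10, outcome SD 1, no true effect, each TAU participant a cluster of one, and a 1.96 reference.

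**3. Expected size of the uncorrected variance.**
- True variance of the CBT mean: [1 + (m − 1)ρ]/25. For TAU: 1/25 = 0.0400.
- Expected sandwich contribution from CBT: (k − 1)/k of its true value. For TAU: (24/25)/25 = 0.0384.

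At ρ = 0.05:

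| k | CBT true | Total true | Sandwich expected | SE ratio |
|---|---|---|---|---|
| 3 | 1.367/25 = 0.0547 | 0.0947 | 0.0364 + 0.0384 = 0.0748 | √(0.0748/0.0947) = 0.89 |
| 4 | 1.2625/25 = 0.0505 | 0.0905 | 0.0379 + 0.0384 = 0.0763 | 0.92 |
| 6 | 1.158/25 = 0.0463 | 0.0863 | 0.0386 + 0.0384 = 0.0770 | 0.94 |
| 8 | 1.106/25 = 0.0443 | 0.0843 | 0.0387 + 0.0384 = 0.0771 | 0.96 |

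Simulation gives 0.88, 0.91, 0.94 and 0.96, in agreement.

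**4. Coverage.** Bias is only part of the loss. With k = 4, an SE ratio of 0.92 alone would give P(|Z| < 1.80) ≈ 93%. The rest comes from the instability of a variance based on so few clusters. Simulated coverage of the nominal 95% interval (40,000 null trials per setting):

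| k | Therapist clusters, ICC 0 | ICC 0.05 | ICC 0.10 | Participant clusters only, ICC 0.05 |
|---|---|---|---|---|
| 3 | 89.8% | 88.5% | 87.7% | 91.3% |
| 4 | 91.1% | 90.1% | 89.8% | 92.0% |
| 6 | 92.4% | 91.8% | 91.8% | 92.7% |
| 8 | 92.8% | 92.5% | 92.5% | 93.2% |

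With only 2 therapists and ICC 0.05, coverage with therapist clusters is 84.9%. The shortfall is present at ICC 0, so it does not depend on assuming a therapist effect.

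Full GEE fits with two follow-ups (within-person correlation 0.5 assumed, ICC 0.05, 500 runs, simulation error about 1.3 points) gave 87.4%, 90.8% and 92.8% for 3, 4 and 6 therapists. Exchangeable model-based standard errors did no better in kind: 88.0%, 91.4% and 93.2%.

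**5. With a correction.** Multiply the CBT variance by k/(k − 1) and the TAU variance by 25/24, giving V₁ and V₀. Use a t reference with df = (V₁ + V₀)² / [V₁²/(k − 1) + V₀²/24]. At ICC 0.05 coverage becomes 93.9%, 94.5%, 94.8% and 95.0% for 3, 4, 6 and 8 therapists. The typical interval is wider by 31%, 22%, 14% and 11%. With 3 therapists the figure is 44% if mean widths are compared, because some intervals become very wide. The Mancl-DeRouen variance with a normal reference gave 92.2%, 94.4% and 95.0% for 3, 4 and 6 therapists in the 500-run fits.

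**6. What this does to planning.** Take an observed effect of 0.8 (assumed), 4 therapists and ICC 0.05. The mean uncorrected SE is 0.891 × 0.303 = 0.27, so the half-width is 1.96 × 0.27 = 0.53 and the lower limit 0.27. Widened by 22%, the half-width is 0.65 and the lower limit 0.15. A sample size set on the lower limit would differ by (0.27/0.15)² ≈ 3.2 times. The article does not say which point of the interval it will use, so this shows sensitivity only.

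**The case against.** The strongest reply is that the quoted sentence is not itself wrong. It does not say that the standard errors are robust, that therapist is the cluster unit, or that no correction is used. A journal article normally leaves such details to an analysis plan, which is not shown here. A bias-corrected GEE would fit the same sentence. This stands, and it is why the point is conditional.

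The size also depends on figures that the article does not give. With 6 to 8 therapists the loss is only 2 to 3 points of coverage. For participant-level clustering, part of the shortfall is generic: at ICC 0 that approach already rejects in about 6.1% of null trials, so therapist clustering at ICC 0.05 adds only about 1 to 2 points.

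The analyses are declared exploratory, and the main stated aims concern feasibility matters such as recruitment, retention and missing data. Over-rejection therefore has little direct consequence. Exploratory status does not remove the need for an honest interval, though, and this one has a stated planning use.

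A reader might also infer a far larger error by supposing that all TAU participants share one no-therapist cluster. Nothing in the article proposes that coding, so it should not count towards the size. A further argument, that GEE is biased under informative dropout, is a separate matter. It was not quantified, and the article plans to record the extent and distribution of missing data.

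**Conclusion.** The point holds in conditional form, with moderate severity. The article pairs a large-sample method with a clustering structure that has few clusters, all in one arm. Each conventional uncorrected implementation that was checked under-covers: by roughly 2 to 7 points for 3 to 8 therapists across ICC 0 to 0.10 with therapist clusters, and by about 2 to 4 points at ICC 0.05 with participant clusters only. These sizes rest on assumed numbers of therapists, assumed ICCs and near-equal caseloads.

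A reader might conclude that the trial's intervals will be invalid, or that GEE has to be replaced. The document supports neither conclusion. It does not rule out a correction, and a corrected GEE performs acceptably with 3 or more therapists. This goes beyond missing detail because the named method fails in its default form, a better version is available, and the resulting interval feeds the design of the full-scale trial.

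**What to change.** State the number of therapists and how therapist enters the model, and choose one of two routes.

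- **Keep GEE.** Cluster on therapist in the CBT arm, keep each TAU participant as a singleton cluster, and use a small-sample corrected variance with a Satterthwaite-type t reference. This route was checked and restores about 94 to 95% coverage with 3 or more therapists. With 2 therapists it reaches only about 92% at ICC 0.05.
- **Use a partially nested linear mixed model.** Include a participant effect, a therapist effect in the CBT arm only, and small-sample degrees of freedom. The performance of this model was not simulated. With so few therapists the therapist variance will often be estimated as zero: a simple variance-components estimate at ICC 0.05 was zero or negative in 47 to 50% of simulated trials with 3 to 8 therapists. The plan should say what happens then.

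The cost is a sentence or two in the analysis section and possibly software other than SPSS v16. Intervals become about 11% wider with 8 therapists and about 30 to 45% wider with 3. That extra width is real uncertainty and should be carried into planning the full-scale trial. The article reports 25 of 50 participants recruited, so the change could be made before analysis.
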